## Abstract

**Background:**

The purpose of the predictors for major cardiovascular outcomes in stable ischaemic heart disease (PREMAC) study is exploratory and hypothesis generating. We want to identify biochemical quantities which—conditionally on the values of available standard demographic, anamnestic, and biochemical data—may improve the prediction of cardiovascular outcomes and/or death in patients suffering from stable ischaemic heart disease. The candidate biochemical quantities include N-terminal pro-B-type natriuretic peptide, YKL-40, osteoprotegerin, high-sensitive assay cardiac troponin T (hs-cTnT), pregnancy-associated plasma protein-A (PAPP-A), cathepsin B, cathepsin S, soluble TNF receptor 1 and 2, neutrophil gelatinase-associated lipocalin, endostatin, and calprotectin. As an extra objective, we also want to assess if skewness in these predictors may explain why the clarithromycin for patients with stable coronary heart disease (CLARICOR) trial found increased all-cause and cardiovascular (CV) mortality on a brief clarithromycin regimen compared with placebo.

**Methods:**

Baseline data were obtained from the hospital files at five cardiology clinics covering the Copenhagen area. The CLARICOR trial included data from 4372 stable coronary artery disease patients recruited among such patients alive and diagnosed with acute myocardial infarction or unstable angina pectoris during 1993 to 1999 in Copenhagen and randomised during October 1999 to April 2000 to the CLARICOR trial of 14 days clarithromycin versus placebo.

Initial follow-up lasted for 2.6 years, during which outcomes were collected through hospital and death registries and assessed by an adjudication committee. Corresponding register data later showed to produce similar results. The adjudicated outcomes were therefore replaced and augmented by register data on outcomes to cover 10 years of follow-up. Biochemical marker data were obtained from analysis of serum from the CLARICOR bio-bank collected at randomisation and stored at −80° C.

Using Cox proportional hazard method, we will identify among the candidate biochemical quantities those which are significant predictors when used alone and in combination with the standard predictors as defined in the present study.

**Discussion:**

Patients who became stable during the period 1993 to 1999 and died before October 1999 are missing. The data from the placebo patients are nevertheless useful to identify new prognostic biomarkers in patients with stable coronary artery disease, and data from both trial groups are useful to assess important potential skewness between randomised groups. However, due to the potential selection bias, we do not feel that it is advisable to try to rank identified biochemical predictors relative to each other nor to use the results for predictive purposes.

**Trial registration:**

ClinicalTrials.gov, NCT00121550

Date of registration 13 July 2005

Date of enrolment of first participant 12 October 1999

## Background

Cardiovascular diseases, and ischaemic heart disease in particular, affect large fractions of the elderly population and constitute one of the two dominant causes of death [1–5]. Identifying high-risk patients would allow one to assess more aggressive measures for treatment of cardiovascular disease [6]. The Prognosis Research Strategy (PROGRESS) series introduced a framework of four themes [7–9], including identification of specific factors (such as biomarkers and treatment modalities) that are associated with prognosis (prognostic factor research). This theme is the focus of the present “predictors for major cardiovascular outcomes in stable ischaemic heart disease” (PREMAC) study.

## Methods

### Objectives of the PREMAC study

Our primary objective is to identify biochemical predictors of a combined outcome including acute myocardial infarction (AMI), unstable angina pectoris (UAP), cerebro-vascular disease (CeVD), cardiovascular mortality (CV death), and all-cause mortality in non-hospitalised patients with stable coronary artery disease.

### The patient group and data material

The patient group comprises the patients who participated in the clarithromycin for patients with stable coronary heart disease (CLARICOR) trial [10, 11], and the data material includes the baseline data collected at randomisation augmented by biomarker data obtained by analysing the bio-bank material collected at baseline and outcome data prospectively obtained from public registers [12].

#### The patients

The patient group is defined by the inclusion and the exclusion criteria of the patients who, during the winter 1999–2000, entered the CLARICOR trial.

The CLARICOR trial was an investigator-initiated, randomised, placebo-controlled, multicentre superiority trial including outpatients with stable coronary artery disease (CAD), using central 1:1 randomisation and blinding of all parties. All patients discharged from wards or outpatient clinics in the Copenhagen area were available in an existing database. We invited all 13,702 patients who were alive and aged 18–85 years in 1999 and identified with a diagnosis of myocardial infarction or unstable angina pectoris during the years 1993–1999 to visit one of five cardiology centres in the Copenhagen area. Six thousand one hundred sixteen (44.6%) patients accepted the invitation, and of these, 4372 (71.5%) were randomised, while 1567 (25.6%) were excluded, and 177 (2.9%) refused to participate. Exclusion criteria included AMI or UAP within the previous 3 months, percutaneous transluminal coronary angioplasty and coronary bypass surgery within the previous 6 months, impaired renal or hepatic function, congestive heart failure (New York Heart Association (NYHA) IV classification of heart failure), active malignancy, incapacity to manage own affairs, breast feeding, and possible pregnancy. Between October 1999 and April 2000, the 4372 patients were randomised to receive oral clarithromycin 500 mg once daily for 2 weeks versus matching placebo to assess the effects on the risk of major cardiovascular outcomes and death.

The main results of the CLARICOR trial were that clarithromycin increased the risk of cardiovascular as well as all-cause mortality [12–14].

#### The data

Data material collected from the 4372 patients include (1) demographic and anamnestic (hospital) data gathered prior to the randomisation, (2) values of biochemical quantities measured in plasma specimens obtained from the patients at randomisation, and (3) vital data and diagnostic information on first occurrence of cardiovascular outcomes covering the period from the start of the trial until December 31, 2009, and obtained from public registers.

##### Demographic and anamnestic data

Clinical data were obtained during enrolment interviews (smoking status, current medication, and known hypertension or diabetes), while information concerning sex, age, and history of myocardial infarction or unstable angina pectoris were obtained from the local hospital files.

##### Biochemical measurements on plasma collected at entry

Blood samples on trial participants were obtained just before randomisation and stored at −80° C. The following quantities were later measured: lipoproteins (total cholesterol, HDL cholesterol, LDL cholesterol, triglycerides, apoprotein A1, apoprotein B), high-sensitivity c-reactive protein (hs-CRP) [15], YKL-40 [16], high-sensitive assay cardiac troponin T (hs-cTnT) [17], pregnancy associated plasma protein-A (PAPP-A) [18], N-terminal pro-B-type natriuretic peptide [17], cathepsin B [19], endostatin [20], cathepsin S [21], soluble TNF receptor 1 and 2 (sTNFR1 and sTNFR2) [22], neutrophil gelatinase-associated lipocalin (NGAL) [23], calprotectin [24], osteoprotegerin [25], and glomerular filtration rate using creatinine (GFR) [26].

##### Vital data and diagnostic information on cardiovascular and other vascular outcomes

Vital status was monitored via the Danish Central Civil Register. Information about the underlying cause of death was obtained from the National Register of Causes of Death (RCD) [27]. The Danish National Patient Register (NPR), covering all somatic hospital admissions, provided hospitalisation data [28]. A blinded adjudication committee, consisting of three cardiologists, working in randomised rotation, assessed each hospital admission or death, using standard diagnostic criteria during the first 2.6 years of follow-up [10, 29]. These results were later compared to the results obtained when only registry data were used and similar conclusions were reached [29, 30]. The follow-up period was therefore extended to 10 years, and the analysis of the full 10 years period was solely based on registry data [10], as explained in the following.

The Danish 10-digit central person registration (CPR) number is used at all contacts with the health care system. Somatic hospital contact cannot be completed without a diagnosis based upon the International Statistical Classification of Diseases, 10th revision (ICD-10) and subsequent notification of the NPR. Each department must issue at least an action diagnosis (A diagnosis), describing the main reason for the admission. Other important diagnoses may be recorded as B diagnoses. All registers have coverage close to 100%. Based on this material, we used the following algorithm to transform the registry information into CV outcomes: for each A code in discharge notifications and, in case of death, each ‘underlying cause of death’ code (in the official terminology of the Registry of Causes of Death), we classified the outcome according to the ICD-10 coding system into a list of disjoint and exhaustive categories: acute myocardial infarction (AMI) (I21.0–23.9), unstable angina pectoris (UAP) (I20.0, I24.8–24.9), cerebro-vascular disease (CeVD) (I60.0–64.9 and G45.0–46.8), peripheral vascular disease (PVD) (I70.2–70.9), and non-cardiovascular disease (A00.0–T98.3 except the codes already covered).

For each patient and each of the outcomes AMI, UAP, CeVD, CV death, and all-cause mortality, we scanned the discharge codes in chronological order. We began with the codes of the first admission following randomisation and recorded the period from the date of randomisation until the date of the first occurrence of the outcome or (in case of a non-fatal outcome) until the date of death or until the date of censoring (December 31, 2009) whichever came first.

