
### Statistical analysis

Each of the abovementioned advanced biochemical predictors will be studied individually on the below mentioned outcomes provided that the advanced quantity concerned has shown promise in the primary (‘gatekeeper’) analysis. This primary ‘gatekeeper’ analysis will examine a composite outcome, defined to be present if at least one of the events AMI, UAP, CeVD, and all-cause death has occurred in a patient. The analyses will be conducted using the Cox proportional hazard model supplemented by Breslow estimation of the baseline hazard. We will use SAS 9.4, and the analysis will be based on the data from the placebo group because it was previously shown that clarithromycin had a significant and harmful effect on the prognosis of the trial patients [10, 12–14].

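### As printed, the register algorithm labels every circulatory code outside four short lists non-cardiovascular, and CV death has no code list of its own to correct this

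*SAP article*

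**What the plan says.** In the SAP article, the section on vital data and diagnostic information describes how register codes become outcomes. The rule covers deaths as well as admissions: it is applied "for each A code in discharge notifications and, in case of death, each ‘underlying cause of death’ code". The result is described in these words: "we classified the outcome according to the ICD-10 coding system into a list of disjoint and exhaustive categories".

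The classes are AMI, "acute myocardial infarction (AMI) (I21.0–23.9"; UAP, "unstable angina pectoris (UAP) (I20.0, I24.8–24.9"; CeVD, with I60.0–64.9 and G45.0–46.8; and finally "peripheral vascular disease (PVD) (I70.2–70.9), and non-cardiovascular disease (A00.0–T98.3 except the codes already covered".

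The same section says that the 10-year analysis rests on registers alone. It goes on to list CV death among the outcomes for which time to first occurrence is recorded, but gives no codes for it.

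Objectives of the PREMAC study includes CV death in the combined outcome, which ends with "cerebro-vascular disease (CeVD), cardiovascular mortality (CV death), and all-cause mortality". Under Statistical analysis, the gatekeeper composite is present if "at least one of the events AMI, UAP, CeVD, and all-cause death has occurred in a patient". Flow of analyses then takes the selected markers to each individual outcome of that composite.

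**The concern.** A remainder class defined as everything not already listed takes in all circulatory disease that the four lists leave out. The cohort has coronary disease, and The patients lists only NYHA class IV under heart failure as an exclusion, so people with milder failure could enter. Causes such as heart failure, chronic ischaemic heart disease and cardiac arrest are ones a reader would expect to count as cardiovascular.

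Two planned results depend on the line between cardiovascular and other death. The first is the CV-death model, with the discrimination measures planned for the mortality models. Background information on the advanced biochemical predictors describes NT-pro-BNP as a marker of ventricular dysfunction and heart failure, so placing heart-failure deaths on the non-cardiovascular side changes what a CV-death hazard ratio for that marker means. The second is the re-analysis under Supplementary exploration, which asks whether chance imbalance explains the higher cardiovascular and all-cause mortality on clarithromycin.

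**Working it through.** The plan states no figure for this point, so the check is to apply the printed code ranges literally: the four named lists first, then the remainder A00.0–T98.3.

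**Inputs** (all from the section on vital data and diagnostic information): AMI I21.0–I23.9; UAP I20.0 and I24.8–I24.9; CeVD I60.0–I64.9 and G45.0–G46.8; PVD I70.2–I70.9; remainder, all other codes from A00.0 to T98.3.

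**Step 1. Sample codes.**

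| Code | Class under the printed rule |
|---|---|
| I21.9 (control) | AMI |
| I64.9 (control) | CeVD |
| I70.2 (control) | PVD |
| I25.1, I25.9 (chronic ischaemic heart disease) | non-cardiovascular |
| I46.1, I46.9 (cardiac arrest) | non-cardiovascular |
| I48.9, I49.0 (arrhythmia) | non-cardiovascular |
| I50.0, I50.9 (heart failure) | non-cardiovascular |
| I71.3 (aortic aneurysm) | non-cardiovascular |
| I11.0, I20.9, I24.0, I26.9, I35.0, I42.0, I69.4, I70.0 | non-cardiovascular |

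The controls fall where they should, so the ranges are being read as intended.

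**Step 2. The whole circulatory chapter.** Running through I00.0–I99.9, only 11 three-character numbers have any code in a cardiovascular class: I20–I24, I60–I64 and I70. Three of these (I20, I24, I70) are covered only in part, which leaves 11 − 3 = 8 covered in full. All other I-codes go to the remainder.

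**Step 3. From classes to CV death.** The article prints no code list for CV death. The only printed rule that handles the underlying cause of death is the one above, and it describes itself as sorting codes "into a list of disjoint and exhaustive categories". If CV death is built from that rule, it can include only deaths coded to AMI, UAP, CeVD or PVD. This step is conditional.

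**Step 4. The upper end of the range.** The remainder stops at T98.3. External-cause codes come after it and have no class, so the list is not exhaustive. No named outcome changes: such deaths still count in all-cause mortality and would not be CV deaths.

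**Step 5. Which outcomes depend on the line.**
- AMI, UAP and CeVD have their own lists and do not change.
- All-cause death needs no cause and does not change.
- The composite under Statistical analysis uses all-cause death and does not change. Every CV death is also an all-cause death, so the composites in Objectives and in Statistical analysis are the same set of events.
- CV death changes if step 3 applies.
- The clarithromycin re-analysis changes if it uses the printed rule.

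**Step 6. Where CV death is analysed.** Flow of analyses sends selected markers to the individual outcomes of the composite. The composite under Statistical analysis does not name CV death, while Objectives and the outcome-scanning paragraph do. Read literally, the follow-on list leaves it out.

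**The case against.** The strongest reply is that nothing here shows how deaths were actually counted. The article describes a classification already carried out and cites the earlier trial reports for it. It also says that register and adjudicated outcomes led to similar conclusions. A cardiovascular remainder may simply have been lost in drafting, and the definition of CV death may stand in those reports, which are not at hand. This stands as a limit: a reader might infer that heart-failure or chronic ischaemic deaths were in fact excluded, and the document does not establish that. It does not remove the point, because the text does not merely omit detail. It assigns these codes to a class named non-cardiovascular and claims to cover everything.

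A second reply is that the effect is contained. The selection of markers starts from a gatekeeper that uses all-cause death, and the study calls itself exploratory. That stands too.

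Three further inferences are tempting and are not supported.
- **A loss of power for CV death.** Any figure would need an assumed number of CV deaths, an assumed share coded outside the lists and an assumed hazard ratio. The article gives none of these, and the main issue is what the outcome means.
- **A changed composite.** Leaving CV death out of the Statistical analysis wording does not alter the composite, since all-cause death contains it.
- **A clarithromycin re-analysis of a different outcome.** Supplementary exploration says the analysis is repeated with markers added, which may keep the earlier definition. A mismatch is possible but not shown.

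**Conclusion.** The point holds for the printed rule. Every circulatory code outside the AMI, UAP, CeVD and PVD lists is assigned to non-cardiovascular disease, and CV death has no definition that overrides this. If the printed algorithm is followed, deaths from heart failure, chronic ischaemic heart disease or cardiac arrest are not CV deaths. The conclusion rests on that condition, and on the algorithm being the only basis for CV death in the article.

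The reach is the CV-death follow-on analysis and, if the same rule is used there, the supplementary CV-mortality re-analysis. The gatekeeper selection is untouched. The number of deaths involved cannot be computed from the document. The external-cause gap is a wording error without effect on a named outcome. The definition should be corrected before CV death is analysed, but it does not threaten the primary selection of markers.

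**What to change.** 1. Add a class for other cardiovascular disease that takes the I00–I99 codes not already in AMI, UAP, CeVD or PVD.
2. Restrict the non-cardiovascular remainder to codes outside all cardiovascular classes (G45–G46 stays in CeVD), and extend it to external causes so that the list is exhaustive.
3. State which classes of underlying cause define CV death.
4. Confirm that this definition matches the one in the earlier CLARICOR register analysis. If it does not, report CV death under both definitions, so that the re-analysis under Supplementary exploration stays comparable with the result it re-examines.
5. Say under Statistical analysis and Flow of analyses that CV death is a follow-on outcome, since the composite as listed does not name it.

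The cost is a change of wording and a re-run of the register classification program. No new data are needed. If the program already has such a class, only the text changes.

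### The follow-up rule has no stop at non-cardiovascular death for the CV-death outcome, so as written its Cox model estimates an undeclared subdistribution-type hazard

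*SAP article*

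**What the plan says.** The rule is in the SAP article, Methods, under Vital data and diagnostic information on cardiovascular and other vascular outcomes.

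- **Scope.** It applies to five outcomes: "For each patient and each of the outcomes AMI, UAP, CeVD, CV death, and all-cause mortality, we scanned the discharge codes in chronological order".
- **End of time at risk.** Time is counted from randomisation and stops when the event in question is first recorded. For patients without that event, the rule reads: "or (in case of a non-fatal outcome) until the date of death or until the date of censoring (December 31, 2009) whichever came first".
- **Event sources.** The preceding paragraph builds the outcome categories from two registers, using discharge A codes and underlying-cause-of-death codes together. Its algorithm opens: "for each A code in discharge notifications and, in case of death, each". Cause of death is available: "Information about the underlying cause of death was obtained from the National Register of Causes of Death (RCD").
- **Model.** Under Statistical analysis: "The analyses will be conducted using the Cox proportional hazard model supplemented by Breslow estimation of the baseline hazard". Neither that section nor any other says how death from another cause is handled when CV death is the outcome.
- **Gatekeeper.** The composite is "defined to be present if at least one of the events AMI, UAP, CeVD, and all-cause death has occurred in a patient".
- **Absolute risks.** Illustration of predictive impact plans 3-, 6- and 9-year risks per patient from the same Cox-Breslow fit.

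**The concern.** The parenthesis lets death end follow-up only for non-fatal outcomes. That works for AMI, UAP and CeVD, where death is a stop, and for all-cause mortality, where every death is the event. CV death is the mixed case. A patient who dies of cancer in 2001 has had no CV death, and the stop at death does not apply. As written, this patient contributes time at risk of CV death to 31 December 2009.

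A Cox model on times built that way does not estimate the cause-specific hazard. It estimates something close to a subdistribution hazard, because non-CV deaths stay in the risk set and censoring is almost all administrative (the Discussion reports 0.5% lost to follow-up). On that scale, a marker that raises non-CV death has its CV-death HR pulled down, even if its association with CV death among the living is unchanged.

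The condition for this shift is not hypothetical here. Background information on the advanced biochemical predictors reports that NT-pro-BNP, a candidate, predicted non-cardiovascular as well as cardiovascular death in patients with coronary disease, with similar results for YKL-40. The CV-death HRs would also be set beside AMI, UAP and CeVD HRs that are cause-specific, with nothing to tell the reader that the scales differ.

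**Working it through.** **Step 1. Apply the rule outcome by outcome, for a patient who dies of a non-CV cause before the end of 2009 with no earlier event.**

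| Outcome | Is the death the event? | Does the parenthesis stop time at death? | End of time as written |
|---|---|---|---|
| AMI, UAP, CeVD | no | yes (non-fatal outcome) | date of death |
| All-cause mortality | yes | not needed | date of death |
| CV death | no | no (fatal outcome) | 31 December 2009 |
| Gatekeeper composite | yes (all-cause death is a component) | not needed | date of death at the latest |

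Only the CV-death row goes wrong.

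**Step 2. Illustrate the size.** The article states no event counts or rates for this outcome, so there is no figure of its own to reproduce. Inputs:

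- From the article: n = 2199 placebo patients. Follow-up is 9.67 to 10.22 years (entry between 12 October 1999 and the end of April 2000, to 31 December 2009); 9.9 years was used for all.
- Assumed: 10-year risks of CV/non-CV death at the marker mean of 15/15%, 20/20% and 20/30%; constant cause-specific hazards; one standardised marker.

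Hazards: H = −ln(1 − total risk), shared between causes in proportion to their risks and divided by 9.9. For 20/20%, H = −ln(0.60) = 0.511, so each hazard is 0.511 × 0.5 / 9.9 = 0.0258 per year.

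In each of 200 simulated cohorts per setting, the CV-death Cox model was fitted twice: with time ended at non-CV death, and with non-CV deaths kept at risk to 9.9 years.

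| Marker HR: CV death / non-CV death | Time ended at non-CV death | As written, 15/15% | As written, 20/20% | As written, 20/30% |
|---|---|---|---|---|
| 1.3 / 1.0 | 1.30 | 1.295 | 1.297 | 1.297 |
| 1.3 / 1.3 | 1.30 | 1.268 | 1.251 | 1.226 |
| 1.3 / 1.6 | 1.30 | 1.235 | 1.205 | 1.160 |
| 1.0 / 1.5 | 1.00 | 0.961 | 0.951 | 0.918 |

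The added person-time, after death, is 9.5–10.3%, 14.0–15.1% and 23.2–24.8% in the three settings.

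**Step 3. Set this against sampling error.** With about 2199 × 0.15 = 330 CV deaths, the standard error of the log HR per SD is roughly 1/√330 = 0.055. With 2199 × 0.20 = 440 it is 0.048. The shift from 1.30 to 1.235 is 0.262 − 0.211 = 0.051 on the log scale, about one standard error. The shift to 1.160 is 0.262 − 0.148 = 0.114, more than two. Even so, 0.148/0.048 = 3.1 exceeds the 2.58 needed for P < 0.01, so a marker with a cause-specific HR of 1.30 would usually still be selected. Weaker markers are the ones that could drop out. In the last row, ln(0.918)/0.048 = −1.8, so a spurious protective effect would not usually reach P < 0.01. These standard errors ignore adjustment for the standard predictors, which would enlarge them.

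**Step 4. Consequence for absolute risks if time is ended at non-CV death.** At the marker mean, one minus the exponential of the cumulative CV hazard gives 1 − 0.70^0.5 = 16.3%, 1 − 0.60^0.5 = 22.5% and 1 − 0.50^0.4 = 24.2%. The actual risks in the three settings are 15%, 20% and 20%. Correcting the HR scale alone would therefore leave the Cox-Breslow risks of CV death too high.

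**The case against.** **It may be loose drafting.** The parenthesis may only be meant to separate outcomes stopped by death from outcomes that are deaths, overlooking the mixed case. The text is in the past tense and summarises a derivation already made. No section says that non-CV deaths were deliberately followed to 2009. This stands. A reader might infer that the data set does hold dead patients at risk, but the article does not show that. It shows only that the stated rule leads there and that nothing else in the text corrects it.

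**A subdistribution hazard is legitimate.** With administrative censoring, keeping competing deaths in the risk set gives a recognised estimand, and its Breslow risk estimates cumulative incidence directly. This also stands, so pulled down is meant relative to the cause-specific hazard. But the article names an ordinary Cox model, declares no such estimand, and uses the other scale for AMI, UAP and CeVD.

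**Reach is limited.** Markers advance only through the composite, which is untouched, and the study is described as exploratory. This is right and limits the weight of the point.

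**A stronger reading to resist.** Because the rule says "we scanned the discharge codes in chronological order", a reader might infer that a fatal AMI or stroke without an admission is censored rather than counted. The article does not support that. The paragraph before sends underlying-cause-of-death codes as well as discharge codes through the same step: "we classified the outcome according to the ICD-10 coding system into a list of disjoint and exhaustive categories". The scanning sentence also covers CV and all-cause death, which discharge diagnoses cannot supply, so discharge codes must be shorthand there. No loss of AMI or CeVD events follows.

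**Conclusion.** The point holds for the CV-death outcome only. As written, the rule leaves non-CV deaths in the CV-death risk set to the end of 2009, which turns that analysis into an undeclared subdistribution-type one and puts its HRs on a different scale from AMI, UAP and CeVD.

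Its size depends on rates that the article does not give. Under the assumed risks, a cause-specific HR of 1.30 reads as about 1.23–1.27 or 1.16–1.24 when the marker's non-CV-death HR is 1.3 or 1.6, and does not move when the marker is unrelated to non-CV death. It is a secondary-outcome correction worth making before analysis. It casts no doubt on the gatekeeper selection or on all-cause mortality.

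**What to change.** 1. **Follow-up rule.** State that for the CV-death HRs, as for the other outcomes, time ends at first occurrence, death from any cause or 31 December 2009, whichever comes first. Alternatively, declare expressly that a subdistribution hazard is intended for CV death, and say that its HRs are not on the scale of the others.
2. **Absolute risks.** If time ends at non-CV death, say under Illustration of predictive impact that the 3-, 6- and 9-year CV-death risks allow for competing non-CV death, for example by combining cause-specific Cox models for CV and non-CV death into a cumulative incidence.
3. **Wording only.** Make the scanning sentence name both discharge A codes and underlying-cause-of-death codes, to match the paragraph before it.

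The cost is a few sentences in the SAP article, a check of how the CV-death time variable was derived and, if it followed the literal rule, a re-derivation. Item 2 adds one further model for non-CV death. Dates and causes of death are already held from the registers, so no new data are needed.
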